## Objectives

This current protocol describes a feasibility study using a cluster randomized controlled trial (c-RCT) design. The pilot study compares implementation as usual for mental health services to the SCAPE-U implementation strategy, in which PWLP collaborates in training primary care workers and community health workers, as well as conducting home visits to service users and their families. The pilot and feasibility study have the following objectives (see Table 1):To assess the feasibility and acceptability of involving people with lived experience of psychosis in mental health trainings and home visits.To determine recruitment and retention rates of SCAPE-U facilitators, service users and their caregivers, primary care workers, and community health workers.To establish the acceptability and feasibility of data collection procedures.To demonstrate the feasibility of trial procedures.To demonstrate the ethics and safety of the study procedures.To describe changes in outcome measures at individual, family, and health system levels.To determine the cost of the SCAPE-U implementation strategy.

**Table 1 Tab1:** Feasibility trial objectives

**Objective**	**Resear**ch questions	**Hypothesis**	**Methods**	**Participants**
**1. Feasibility and acceptability of SCAPE-U**	Is it feasible to train and involve people with lived experience of psychosis in the intervention? Do primary care workers, community health workers and caregivers of service users find it acceptable to have people with lived experience of psychosis as co-facilitators in their trainings/supervision and home visits?	People with lived experience of psychosis can be trained to deliver training and home visits effectively and safely All the key stakeholders of the intervention will find the involvement of people with lived experience acceptable	Qualitative interviews Process notes Adverse event logs (target: fewer than 20% among recruited PWLE)	SCAPE-U facilitators, primary care workers, community health workers, service users and their families, research staff and trainers

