**5. Ethics and safety**	Can SCAPE-U be delivered with best ethical practice and safety of SCAPE-U facilitators, primary care workers, community health workers, service users and their families? Are there any unintended harms and how can they be addressed?	SCAPE-U intervention can be delivered with minimum harm to all stakeholders	Qualitative interviews Adverse event log Process notes	SCAPE-U facilitators, primary care workers, community health workers, service users and families, research staffs
**6. Change in outcome measures**	Do the outcome measures of the stakeholders improve after participating in the intervention?	Stakeholders in the SCAPE-U intervention arm will exhibit better outcomes than in control arm	Outcome measures assessment	Primary care workers, community health workers, service users and families
**7. Cost of intervention**	Can we measure the cost of SCAPE-U using measures and procedures from this study?	Costing of the intervention can be done in subsequent trial using procedures and measures tested in this pilot study	Cost-related outcome measures	YouBelong team, primary care workers, community health workers, service users and families

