### Study participants

This study will involve six categories of study participants:(i)People with lived experience of psychosis trained as SCAPE-U facilitators—8 to 10 people with lived experience of psychosis who have previously received services from YouBelong Uganda [33, 35] will be recruited. The inclusion criteria are (1) diagnosis of a psychotic disorder confirmed by a mental health professional (psychiatric clinical officer or psychiatrist). (2) Capacity to provide informed consent. The main exclusion criterion is any health, functional, or cognitive impairment, assessed through mental state examination, that could jeopardize their full and safe participation in SCAPE-U activities. There are no inclusion/exclusion criteria relating to current engagement in treatment.(ii)Primary care workers—two primary care workers will be selected per health facility, with a target of 36 primary care workers per arm (72 total for the study). There are no exclusion criteria.(iii)Community health workers—we will select up to five community health workers from each health facility. This will equate to approximately 90 community health workers per arm and an estimated total of 180 community health workers for the study.(iv)Psychiatrists, psychiatric clinical officers,and psychiatric nurses—1 psychiatrist, 3 psychiatric clinical officers, and 2 psychiatric nurses who are involved in delivering training to primary care workers will be included.(v)Service users diagnosed with psychosis by primary care workers—the primary intended beneficiaries of study interventions are service users receiving treatment for psychosis at primary care facilities. The goal is to have 10 service users per cluster, 30 per arm, and 60 in total for the study. *Inclusion criteria*: (1) persons diagnosed with psychosis at a primary health care facility in Kampala/Wakiso District, following mhGAP training as part of the SCAPE-U trial; (2) ability of the service users to consent to study enrollment and procedures, or, if the service user does not have capacity to consent, a responsible surrogate can give consent; (3) persons eligible for outpatient management of psychosis. *Exclusion criteria*: (1) persons diagnosed with psychosis requiring inpatient management; and (2) persons for whom consent for participation in the study cannot be obtained.(vi)Family members of service users—at least one primary carer for study service users will be identified to collect outcome data from a family perspective (*n* = 30 per arm, 60 for the total study).

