### Randomization and blinding

Randomization of clusters in the feasibility trial will be completed prior to participant recruitment and will be conducted by an independent statistician using Stata. Covariate-constrained clusterrandomisation will be used to assign health facility clusters to study arms while ensuring balance across key variables {Hemming, 2023 #120}[48]. Covariate-constrained randomization is a form of restricted randomization; specifically, the randomization will be constrained on two characteristics: number of health facilities per arm, and rural vs. urban location.

Constrained randomisation helps prevent baseline imbalances that can occur by chance, particularly in studies with a limited number of clusters, such as feasibility trials [48]. For logistical reasons, research assistants/data collectors will not be blinded. PCWs and CHWs will be blinded to the arm allocation. We will have separate mhGAP-IG trainers for each arm, and these will be blinded. Because SCAPE-U facilitators will be engaged only in the intervention arm, and only service users accessing care at PHCs in the intervention arm will receive the home visit intervention, they will both be blinded by the cluster randomized nature of the trial.

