### Measures/outcomes for feasibility criteria and other objectives

The primary outcome of this trial is to understand the feasibility and acceptability of the SCAPE-U intervention. We have developed a set of quantitative and qualitative measures to do this as guided by recommendations from pilot study reporting [49]. These measures will determine what components of the SCAPE-U intervention will be included, excluded, or modified in the future full trial. The following quantitative criteria have been set to determine if this feasibility trial can be scaled up for a fully powered trial.Recruitment: at least 2 primary care workers were recruited in the study from each of the 36 health facilities selected.Retention: 50% of SCAPE-U facilitators retained by the end of PhotoVoice training, 60% of primary care workers, 60% of community health workers retained in post until the end of the 8 months follow-up period, and 50% of service users and families retained by the end of 5 session home visits.Contamination: less than 20% of cross-arm movement of primary care workers, community health workers, service users, and their families during the 8-month follow-up period.Cluster comparison: measuring baseline characteristics of recruited primary care and community health workers across both arms. We will collect information on primary care workers and community health workers’ education qualifications, gender, prior mental health training, age, and years of experience and determine balance between arms.Data collection procedure: less than 20% of missingness in collected data.Safety: fewer than 20% of adverse events among recruited SCAPE-U facilitators and service users.

Our qualitative criteria for this feasibility study are presented in Table 3.

**Table 3 Tab3:** Assessment of feasibility and acceptability of the intervention and trial procedures

Domains	Research questions	Methods
Feasibility and acceptability of SCAPE-U intervention	Do psychiatrist/psychiatric clinical officer, primary care workers, and mental health service users find it feasible and acceptable for PhotoVoice trained people with lived experience to participate as co-facilitators in training and supervision?	● Qualitative interviews with psychiatrist/psychiatric clinical officer, primary care workers, SCAPE-U facilitators, and research staff ● Process notes from trainings and supervision sessions

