Symptoms of psychosis	Positive and Negative Symptoms of Schizophrenia (PANSS) scale	Adapted scale for self-report	PWLP as SCAPE- U facilitators	
Service users with psychosis diagnosed by primary care workers				
Symptoms of psychosis	Positive and Negative Symptoms of Schizophrenia (PANSS) scale	Adapted scale for self-report (or report by a family member)	Service users or family members	Baseline, 4 and 8 months follow-up
Quality of life	World Health Organization Quality of Life-Brief version (WHOQOL-BREF)	Self-report scale	Service users	Baseline, 4 and 8 months follow-up
Quality of life (for health economics analyses)	EuroQoL 5-Dimension 5-Level (EQ-5D-5L)	Self-report scale	Service users	Baseline, 4 and 8 months follow-up
Stigma experienced by persons living with mental illness	Discrimination and Stigma Scale-Brief version (DISCUS)	Self-report scale	Service users	Baseline, 4 and 8 months follow-up
Social inclusion	Social Inclusion Scale (SIS)	Self-report scale	Service users	Baseline, 4 and 8 months follow-up
Hospitalization	# days hospitalized during study period	Self-report, family report, and/or hospital records	Service users or family members	4 and 8 months follow-up
Costs of services received	Client Service Receipt Inventory (CSRI)(54)	Self-report and/or family report	Service users or family members	4 and 8 months follow-up
Family members and caregivers of service users				
Impact on family members	Family Interview Schedule—Impact on Caregivers (FIS-IC) (56)	Family report	Main caregiver	Baseline, 4 and 8 months follow-up
Community health workers				
Attitudes towards people with psychosis	Social Distance Scale (SDS)	Self-report scale	Community health worker	Pre- and post-training
Accuracy of psychosis detection	Community health worker referral tool	Percent of community health worker referred patients who meet SCID criteria	Community health worker	Post training
# of individuals referred	Community health worker referral tool	Numbers	Community health worker	Throughout study
# of individuals referred by CHWs who receive a diagnosis of psychosis from PCP	Health facility records	Numbers	Research assistant reviewing clinical records	Throughout study
Primary care workers				
Outcomes	Instrument or data collection strategy	Type of data	Respondent or source	Assessment period
Attitudes towards people with psychosis	Social Distance Scale (SDS)	Self-report scale	Primary care workers	Pre- and post-training, and at final supervision session

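### The 20% safety criterion for scale-up is not limited by seriousness or cause and is not read against the control arm, so it partly measures background illness and weights mild and grave events alike

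*Protocol article*

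**What the plan says.** The section on measures and outcomes for feasibility criteria introduces its list with "The following quantitative criteria have been set to determine if this feasibility trial can be scaled up for a fully powered trial". The safety entry reads "Safety: fewer than 20% of adverse events among recruited SCAPE-U facilitators and service users". It does not restrict events by seriousness, severity or relation to the study, and it names no comparator. It does not say whether service users means one arm or both, or whether the percentage counts people or events.

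Table 1, objective 1, gives the same figure for a different group: "Adverse event logs (target: fewer than 20% among recruited PWLE". In context this most naturally means the facilitators. Objective 5 in the same table states the hypothesis that "SCAPE-U intervention can be delivered with minimum harm to all stakeholders".

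The groups concerned are "8 to 10 people with lived experience of psychosis who have previously received services from YouBelong Uganda", to be trained as facilitators, and service users, for whom "The goal is to have 10 service users per cluster, 30 per arm, and 60 in total for the study". Service users are assessed at "Baseline, 4 and 8 months follow-up" (Table 4). Under Randomization and blinding, "SCAPE-U facilitators will be engaged only in the intervention arm", so facilitators have no control counterpart.

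Safety is also covered elsewhere: a qualitative ethics and safety domain (Table 3), the Service Users Collaboration Checklist (SUCC) and support arrangements (Possible harm and safety), and a DSMB working under standard operating procedures (Trial oversight). None of these is written as overriding the 20% line.

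**The concern.** Service users are outpatients with psychosis who receive medication and are followed for 8 months. Some adverse events will occur in both arms whatever SCAPE-U does. A fixed ceiling on any adverse event, with no qualifier and no comparator, cannot separate those events from harm caused by the strategy. The result also depends on how diligently events are logged.

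Because every event has the same weight, a few mild events can breach the line while one grave event meets it. The Possible harm and safety section itself expects some manageable distress among facilitators. If that distress is logged as an adverse event, two mild cases are enough to breach the ceiling at any planned number of facilitators.

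Safety is named in the abstract as a primary outcome, and this is its only quantitative progression rule. At stake is whether the figure carried into the scale-up decision answers objective 5.

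**Working it through.** The 20% figure is stated without derivation or background rate, so there is nothing to reproduce. The check is how the line behaves when SCAPE-U adds no harm.

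**Inputs from the protocol article:** 8 to 10 facilitators; 30 service users per arm, 60 in total; ceiling strictly below 20%.

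**Assumptions:** the percentage counts people with at least one event; people are independent and share one background risk p; p = 10%, 20% or 30%, because the documents give no rate.

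**Step 1, largest passing count.** m is the largest whole number with m/n < 0.20.
- n = 8, 9, 10 (facilitators alone, the Table 1 reading): m = 1. One affected person is 12.5%, 11.1% or 10.0% and passes; two are 25%, 22.2% or 20.0% and do not.
- n = 38 to 40 (facilitators plus 30 SCAPE-U service users): m = 7.
- n = 68 to 70 (facilitators plus 60 service users in both arms): m = 13.

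**Step 2, chance of missing the target with no intervention effect.** P(miss) = P(X ≥ m + 1), X ~ Binomial(n, p). For n = 10 and p = 0.20: 1 − 0.8^10 − 10 × 0.2 × 0.8^9 = 1 − 0.107 − 0.268 = 0.624.

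| Group | n | p = 10% | p = 20% | p = 30% |
|---|---|---|---|---|
| Facilitators | 8 | 18.7% | 49.7% | 74.5% |
| Facilitators | 10 | 26.4% | 62.4% | 85.1% |
| Facilitators + SCAPE-U service users | 38 | 3.2% | 50.0% | 92.1% |
| Facilitators + SCAPE-U service users | 40 | 4.2% | 56.3% | 94.5% |
| Facilitators + both arms | 68 | 0.7% | 50.0% | 97.0% |
| Facilitators + both arms | 70 | 0.9% | 54.8% | 97.8% |

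At p = 5% the chance is 8.6% for n = 10 and 0.1% or less for n = 40 and n = 70. If events are counted instead of people, repeat events make a miss more likely.

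**Step 3, one serious event.** A single serious facilitator event, as the only event, is between 1/70 = 1.4% and 1/8 = 12.5%. It meets the line under every reading.

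**Step 4, what the control arm can add.** With 30 per arm and 20% in each, the 95% half-width for the difference is 1.96 × √(2 × 0.20 × 0.80 / 30) = 1.96 × 0.103 = 0.202, about 20 percentage points. With three clusters per arm, any allowance for clustering widens it.

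**The case against.** **Unshown documents.** The article only omits a definition; it does not state that events count whatever their severity or cause. Standard operating procedures and a DSMB protocol are mentioned and not shown, and a condensed article may leave definitions to them. This stands as far as the definition goes. But a definition held there would not by itself restrict a criterion printed without qualifier, nor would it add a comparator.

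**A grave event passing.** A reader might infer that a suicide attempt by a facilitator would be declared safe. The documents do not support that. The feasibility section uses qualitative measures alongside the quantitative ones, Table 3 has its own safety domain, and an independent DSMB monitors adverse events. The event would meet one line of a wider assessment.

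**A harmless strategy stopped.** A reader might also infer that missing 20% ends the programme. The Discussion says that problems, including with safety, lead to modification, with an internal pilot in the full trial if changes are large.

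**Size.** The criterion names a combined group. On the combined readings the chance of a false miss is small at a 10% background risk (about 4% or 1%) and negligible at 5%. This stands: the problem becomes large only if the background risk is near 20% or more, or if facilitators are judged alone.

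**Remedy.** The arm comparison is imprecise, and serious events of any cause still include background illness. Both are true, which is why service-user events should be shown by arm and read descriptively. Data collectors are unblinded and only the SCAPE-U arm has home visits, so detection may differ by arm. That affects a fixed any-event percentage too, and should matter less for serious events.

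**Conclusion.** The concern holds for this one criterion. As printed, the line is not limited by seriousness or cause and is not set against the control arm. It therefore partly measures background illness, and it gives events of very different gravity the same weight.

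Its size depends on a background risk that the documents do not give. With no intervention effect, the chance of missing the target is about even or worse from an assumed 20% upward under every reading. At 10% it is about 1% to 4% for the combined groups and about 19% to 26% for 8 to 10 facilitators alone. These figures count people, assume independence and apply one common risk.

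The finding does not extend to the safety oversight as a whole, which has other parts that would see a serious event. Separately, Table 1 and the feasibility section give the 20% target for different populations and must be reconciled.

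**What to change.** - Keep logging and reporting all adverse events, and base the quantitative progression criterion on serious adverse events. Cite the definition used and say whether people or events are counted.
- For service users, tabulate all and serious events by arm with confidence intervals. Read the SCAPE-U rate descriptively against control, not against a fixed any-event percentage.
- For facilitators, who have no control group, report serious events and the unintended consequences recorded on the SUCC. State that each serious facilitator event goes to the existing DSMB for individual review and is not cleared by a percentage.
- Reconcile the population in Table 1, objective 1, with that in the feasibility section, and say whether service users means one arm or both.

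The cost is rewording one criterion, aligning one table entry and adding one table. The adverse event log, SUCC and DSMB are already planned. The downside is precision: at 30 per arm the comparison informs judgement and is not a test, which fits a pilot that disclaims formal hypothesis testing.

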## Interventions

### Standard training and mental healthcare implementation (control arm)

#### Primary care level

Primary care workers will be trained to screen, assess, diagnose, and treat psychosis and related disorders using the WHO mental health Gap Action Programme Intervention Guide (mhGAP-IG, version 2.0) [38]. The mhGAP-IG has been used as a package for providing mental health care in LMIC settings including Uganda [39]. This 5-day training, coordinated by YouBelong Uganda in collaboration with Butabika National Mental Hospital and the Ministry of Health in Uganda, will be delivered by psychiatrists and/or psychiatric clinical officers trained as mhGAP-IG trainers. Training will be delivered primarily in English. After the training, the primary care workers will receive monthly supervision from a psychiatric clinical officer or psychiatric nurse. This is comparable to the standard procedures used nationally for training primary care workers in mental health.

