### Community level

At the community level, community health workers will receive a 2-day training based on the WHO mhGAP Community Toolkit Community Provider manual [40] to increase knowledge and skills required to identify symptoms of psychosis and other mental health problems. Additionally, they will be trained to disseminate information on psychosis at community awareness-raising meetings**.** The training will be delivered in Luganda, the predominant local language, by the trained primary care workers and experienced trainers from the YouBelong Uganda team in collaboration with Butabika Hospital. Community health workers will also receive monthly supervision by trained primary care workers after the training.

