### Primary care level

Primary care workers and community health workers will receive training with the same duration and broad content as the standard implementation (control) arm. However, in the intervention arm, SCAPE-U facilitators will co-facilitate trainings alongside mental health professionals. During the primary care worker training, SCAPE-U facilitators will present sessions on living with psychosis, using their PhotoVoice stories. SCAPE-U facilitators will describe the symptoms of psychosis from an experiential perspective, specifically the experience of suffering, negotiating pathways of care and treatment, including an emphasis on the benefit of psychosocial support in addition to medication. SCAPE-U facilitators will also conduct question and answer sessions so that primary care workers can ask them about their experiences. In addition, SCAPE-U facilitators will be present during the other training sessions so that primary care workers can interact with them in both structured and unstructured social activities. At the conclusion of the training, SCAPE-U facilitators will hold a session on anticipated challenges of primary care workers, and with the primary care workers, they will collaboratively come up with solutions to address these challenges. SCAPE-U facilitators will also collaborate in the supervision of primary care and community health workers after their trainings are completed.

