Fidelity and contagion of intervention	Can fidelity be feasibly and reliably assessed using a fidelity checklist? What degree of fidelity to SCAPE-U is achievable? Can contamination be captured through fidelity and other assessments?	● Qualitative interviews with psychiatrist/psychiatric clinical officer trainers, primary care trainees, SCAPE-U facilitators, and research staff ● Process notes and fidelity checklist from trainings and supervision sessions ● Logs of health workers and service users’ movement across arms
Ethics and safety of trial	Does the research pose harm to primary care workers, service users, or SCAPE-U facilitators, and are these harms adequately prevented, documented, and addressed?	● Qualitative interviews ● Service Users Collaboration Checklist ● Process evaluation notes ● Monitoring of adverse events

*Qualitative data* will be collected from PWLP, primary care and community health workers, service users, and their families, mental health specialists involved in training and research staff involved in data collection through key informant interviews (KIIs) and focus group discussions (FGD). We will conduct KIIs with 75% of the PWLP recruited to be SCAPE-U facilitators and who have completed PhotoVoice training and co-facilitated health workers training and home visits during two timepoints—after the health workers training and after home visits. For those who are just part of the PhotoVoice training, we will conduct an FGD talking about their experiences with PhotoVoice. For PCWs and VHTs, we will conduct KIIs with 15% of the total trained population. Selection will be based on gender, performance based on supervision notes, the number of mental health cases attended, and the level of health facility. We will interview them at 3 months post-training, i.e., during the first supervision. Twenty percent of the service users and their families receiving home visits will be interviewed after the completion of all five sessions. Finally, during the study’s end phase, we will interview all the trainers in both arms and research assistants involved in SCAPE-U data collection.

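### The only health-worker interview is dated both three months after training and at the first supervision, which monthly supervision does not allow; at a first session it would also come before the co-supervision it should assess

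*Protocol article*

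**What the plan says.** The section on measures and outcomes for the feasibility criteria describes the health-worker interviews in three consecutive sentences.

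- Number: "For PCWs and VHTs, we will conduct KIIs with 15% of the total trained population". (The Setting section describes village health teams as made up of volunteer community health workers.)
- Selection: "Selection will be based on gender, performance based on supervision notes, the number of mental health cases attended, and the level of health facility".
- Timing: "We will interview them at 3 months post-training, i.e., during the first supervision".

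The intervention sections state how often supervision takes place. For primary care workers: "After the training, the primary care workers will receive monthly supervision from a psychiatric clinical officer or psychiatric nurse". For community health workers: "Community health workers will also receive monthly supervision by trained primary care workers after the training". Both sentences are in the control-arm description. The intervention arm adds the facilitators without giving another interval: "SCAPE-U facilitators will also collaborate in the supervision of primary care and community health workers after their trainings are completed".

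The question to be answered is in Table 1, objective 1, which asks whether health workers and caregivers "find it acceptable to have people with lived experience of psychosis as co-facilitators in their trainings/supervision and home visits". Table 3 asks whether it is feasible and acceptable "for PhotoVoice trained people with lived experience to participate as co-facilitators in training and supervision", and lists interviews with primary care workers among its methods.

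**The concern.** The timing sentence treats two dates as the same, and under the supervision schedule stated elsewhere they differ by about two months. Interviewers following the protocol would not know which to use.

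The choice matters because feasibility and acceptability form the primary outcome, and the results are meant to decide which components are kept, dropped or modified for the full trial. Co-facilitated supervision is one of those components, and the workers who receive it are among those whose view is sought. Their interview is scheduled once. The end-phase interviews cover trainers and research assistants. The final-session contact in Table 4 applies to primary care workers and collects attitudes to people with psychosis, knowledge, skills, fidelity and diagnostic data; none of these asks about co-supervision. If the single interview comes before the experience it should assess, nothing else in the article obtains the workers' own later view.

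**Working it through.** This is schedule arithmetic. No sample-size, power or error-rate figure is involved.

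**Inputs from the article**
- Interview date: 3 months after training, equated with the first supervision (measures section).
- Supervision interval: monthly after training, for both groups of workers (control-arm sections; no other interval given for the intervention arm).
- Follow-up of workers: 8 months (retention criterion).
- Workers: 72 primary care workers, 36 per arm; about 180 community health workers, about 90 per arm (Study participants).
- Share interviewed: 15%.

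**Assumptions**
- Monthly supervision runs through the 8 months, giving about 8 sessions. The article does not state how long supervision lasts.
- Interviews split evenly by arm. The article does not state this either.

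**Step 1: can the stated date be reproduced?** With monthly sessions, session k falls at about month k, so session 1 is at month 1. If sessions start directly after training, session 1 is at month 0. Neither schedule puts session 1 at month 3. Month 3 is the third session in the first case and the fourth in the second.

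**Step 2: what has a worker experienced at the interview?**

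| Reading | First session | Interview | Sessions completed before it | Sessions after it |
|---|---|---|---|---|
| Monthly; first-session rule governs | about month 1 | about month 1 | 0 | 8 − 1 = 7 |
| Monthly; three-month date governs | about month 1 (month 0 at the earliest) | month 3 | 2 to 3 | 8 − 3 = about 5 |
| Both phrases taken literally; monthly from then on | month 3 | month 3 | 0 | 5 of 6 (months 3 to 8) |

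The third row satisfies the timing sentence only by leaving months 1 and 2 without the monthly sessions that the intervention sections describe.

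**Step 3: can the selection rule be applied?** Selection uses performance recorded in supervision notes. In rows 1 and 3 no session has been completed, so no notes exist from which to choose interviewees. In row 2 notes from two or three sessions exist and the rule works.

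**Step 4: how many interviewees can comment on co-supervision?**
- Both arms: 0.15 × 72 = 10.8, about 11 primary care workers; 0.15 × 180 = 27 community health workers.
- Intervention arm only: 0.15 × 36 = 5.4, about 5; 0.15 × 90 = 13.5, so 13 to 14.

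Control-arm workers receive no co-facilitated supervision and cannot judge it.

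**The case against.** The strongest reply is that only the words about the first supervision are out of place. The three-month date, monthly supervision, and selection on supervision notes and cases attended all fit an interview after two or three sessions. On that reading selection works, workers have met the facilitators in supervision, and Objective 1 can be answered. This stands as a plausible reading, but the text does not confirm it. The sentence states an equivalence, and the article does not show which half is intended.

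Other evidence on supervision is also planned: process notes and a fidelity checklist from supervision sessions, facilitator interviews, monthly facilitator feedback, and end-phase interviews with all trainers. These are partial sources. They do not replace the supervised workers' own view.

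A reader might infer four stronger points, which the article does not support:

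- *That workers' acceptance of co-supervision cannot be assessed at all, with seven of eight sessions never asked about.* This holds only if the first-session rule governs and the three-month date is discarded.
- *That workers cannot speak about treating service users or about home visits.* Identification of service users starts once training is complete, and five fortnightly visits span 4 × 2 = 8 weeks. By month 3 some visit series can be finished, although at month 1 none could be.
- *That workers go unsupervised for three months, distorting the comparison.* The intervention sections say monthly, and no difference in interval between arms is stated.
- *That all interviews must move to the final supervision session.* The retention target is 60%, so up to 40% of workers could have left by 8 months with the target still met. Recall of the training would be weaker, and Table 4 lists no final-session assessment for community health workers.

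**Conclusion.** The timing contradiction is plain on the text: three months and the first supervision cannot be the same date under monthly supervision. Two consequences follow if the first-session rule is carried out. Selection on supervision notes becomes impossible, and workers' only interview precedes the co-supervision they are asked to judge. If the three-month date is carried out, the loss is smaller: the view rests on about 2 to 3 of roughly 8 sessions, with about 5 still to come.

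In either case the relevant evidence comes from about 5 primary care workers and 13 to 14 community health workers. The session counts assume monthly supervision over 8 months, and the interviewee counts assume an even split by arm. The effect is confined to qualitative evidence for the primary acceptability outcome. It should be corrected before the interviews are scheduled, and it does not undermine the design of the trial.

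**What to change.** 1. Reconcile the start and frequency of worker supervision across the control-arm and intervention-arm sections (primary care and community levels) and the interview paragraph of the measures section. The article does not show which timing is intended, so the investigators must settle it.
2. Delete the clause equating the interview with the first supervision.
3. State that worker interviews take place only after several supervision sessions have been completed and documented, so that selection on supervision notes is possible and intervention-arm workers have experienced co-facilitated supervision.

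The change is one of wording and scheduling, with the same number of interviews. The small downside is slightly weaker recall of the training if the interview falls later than it otherwise would. Holding the interviews at the final supervision session is an option, not a requirement.
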